### Telecommunications Technology

Treatment sessions for the Telepsychology condition will be conducted using in-home videoconferencing technology. We will use an analogue videophone (KMEA TV500SP, Figure 2) that operates via plain old telephone service (POTS). Apart from the video screen, this equipment appears and functions much like a basic touch-tone telephone. It is a "plug-and-use" product, with built-in camera, full duplex speakerphone, 4-inch LCD color screen (270 K pixels) with real-time motion display (18 frames per second), and oversized touch-tone buttons for easy use by all patients. This equipment is simple to use. If necessary, project or clinic staff will be available to visit participants in their homes to help set up the equipment. We will track the type and amount of assistance required across sessions in order to help anticipate future difficulties with in-home use.

**Figure 2 F2:**
[figure not shown]
**Videophone**.

### Study Instruments and Data Collection Schedule

Self-report measures will be used to evaluate clinical outcome at baseline, mid-treatment (4-weeks), post-treatment (8-weeks), 3-months, and 12-month follow-up. Process outcomes will be evaluated at 4-weeks, 8-weeks, 3-months, and 12-months. Resource Utilization surveys will be administered at baseline, and then 3 and 12 month follow-up. Endpoint psychiatric interviews (ie, Structured Clinical Interview for DSM-IV, [SCID]) [50]; will be administered at baseline and 12-months by raters blind to subject condition. Structured interviews will be audiotaped, and 20% will be rated by an independent to ensure interrater reliability. The complete assessment takes about 120 minutes. Study assessments will be administered by either the Research Coordinator. Assessment clinicians will not deliver treatment. Their training will include instruction, assigned readings, modeling, role-playing, and feedback.

### Therapist Training and Supervision

The same counselors will conduct the individual BATD treatment for both conditions (Telepsychology, Same-Room). At the start of the project, treatment providers will undergo a 12-hour training program with the clinical psychologist/project consultant and the developer of the BATD treatment manual. During the project, therapists will follow the BATD treatment manual, and will undergo weekly peer supervision with an experienced clinical psychologist on the team. Thus, a highly experienced and expert team of mental health care providers will implement the treatment for the subjects in this study. We have used a similar training approach in our other studies.

### Treatment Integrity and Adherence

A quantitative measure of protocol adherence will be obtained using a checklist of the specific procedures scheduled to be followed in the BATD treatment manual. To ensure treatment adherence, all sessions will be audiotaped, and 20% of these will be rated for competence and adherence by co-investigators. To evaluate adherence to treatment protocol, rating forms that use a 7-point Likert scale were developed and assess how well the therapists accomplished relevant behavioral tasks for each session. Two raters, blind to treatment condition, will rate tapes independently to allow for computation of inter-rater reliability. Our rating forms are modeled after the therapist rating forms used in other studies of cognitive-behavioral treatments, including our own treatment outcome studies that successfully demonstrated therapist fidelity to a manualized cognitive behavioral intervention delivered via "telepsychology" [27]. This will allow us to study any differences between conditions on non-specific factors, such as therapist empathy and rapport.

### Outcome Measures

#### Clinical Outcome Measures

The primary clinical outcome measure is the proportion (%) of patients who respond to treatment. Treatment Responder status will be determined using each of the dependent measures of depression (ie, Geriatric Depression Scale (GDS) [51]; Beck Depression Inventory (BDI) [52]; and SCID [50]. For the BDI and GDS, treatment responders will be those that demonstrate, at 12-month follow-up, improvement of at least 50% on the total score. For the SCID, treatment responders will be those who are no longer diagnosed with MDD. Dichotomous classifications for the GDS and the BDI will be achieved by defining treatment response as at least a 50% improvement from baseline to post-treatment level (percent change from baseline: [baseline-post]/baseline ≥ 50%). We will report analyses involving each measure of treatment response separately, but will take the a priori position that, in the case where results based on each of these analyses do not converge, overall conclusions regarding treatment response will be based on the two measures that concur. Thus, our indicator of treatment response will be in terms of each measure, as well as in terms of the converging data from at least two different measures.

The primary process outcome is score on the Charleston Psychiatric Outpatient Satisfaction Scale (CPOSS), [53] measured at the end of the 12-month follow-up period. The CPOSS is a 16-item measure with each item having a Likert-type format (total score is sum of the 16 items with range 16–80). Non-inferiority of patient satisfaction at the end of the 12-month follow-up period for the two modes of delivery will be evaluated via the one-sided non-inferiority 90% confidence interval approach to estimate the difference in end of study mean scores on the CPOSS for the Telepsychology and Same-Room conditions. The magnitude of the difference in satisfaction levels, as estimated by the confidence interval will provide useful clinical information and will allow a clinical judgment relative to the clinical non-inferiority of the of the two modes of delivery.

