## Methods

The study is a 2 group randomized controlled trial with randomization of individual participants, blinded outcomes assessments at baseline, mid-treatment (4-weeks), post-treatment (8-weeks), 3-months, and 12-months, and concurrent economic evaluation.

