### Sample Size Determination and Power Analysis

The primary response variable for sample size calculation is the proportion (%) of patients who respond to treatment. Treatment response is defined as at least a 50% improvement from baseline to post-treatment level on the GDS [percent change from baseline: (baseline-post)/baseline ≥ 50%]. Demonstration of non-inferiority among treatments differs from that of establishing superiority. For a non-inferiority trial, the null hypothesis states that two treatments are non-equivalent, that is they differ by at least a clinically relevant amount, Δ. [55-62]. The approach will be formulated in terms of the one-sided non-inferiority problem [55,60,61,63] because it is of interest only to test that the treatment response (% responders) for the Telepsychology mode of delivery is not too low compared to that for the standard Same-Room mode of delivery. Note that, for non-inferiority trials, the consequence of a false positive (ie, claiming the novel therapy [Telepsychology] is worse than the standard therapy [Same-Room] when it is, in fact, non-inferior) is to keep patients on the standard therapy. Therefore, the Type I error rate, α, can be set higher than in traditional superiority trials (eg 0.1–0.2) [64].

We estimate that the % treatment responder for Same-Room delivery (P) is 0.70. We assume that a maximum clinically unimportant difference in response proportion (Δ, the non-inferiority effect size) is 0.15 between Telepsychology and the standard Same-Room service delivery (upper limit of one-sided 90% confidence interval must not be greater than Δ = 0.15 for the conditions to be declared equivalent). Using the tables of Machin and Campbell [64] and assuming Δ = 0.15, one-sided α = 0.10, P = 0.70, and power = 0.85, we estimate that approximately n_1 _= n_2 _= 100 subjects per condition are needed for overall treatment effects comparisons. If we further assume that 10% of subjects will not have at least one post baseline measurement (i.e. will not be included in the ITT sample), then 112 subjects must be randomized to each treatment group to yield the required sample size for the primary intent-to-treat analyses (n_1 _= n_2 _= 100/group).

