For the ITT sample (n_1 _= n_2 _= 100/treatment group) we will be able to estimate the individual (main effects) end of treatment means for each of the continuous clinical and process measures with a precision of ± 0.2 standard deviations. For the primary outcome measure Δ_Δ1 _= Δ_(Post)T_- Δ_(Post)S_, which measures the difference in change from baseline (pre to immediate post treatment) for the continuous outcome domain measures for the telepsychology condition compared to change from baseline for the standard (same-room) condition, we will be able to estimate with a precision of ± 0.3 standard deviation units using 95% confidence intervals for the difference in two means (Δ_(Post)T_, Δ_(Post)S_), where the appropriate standard deviation is the pooled standard deviation for comparing change from baseline for the telepsychology condition versus the standard condition.

Assuming that 20% of subjects will drop out of the ITT sample (n_1 _= n_2 _= 80, assuming equal treatment distribution of dropouts), we will be able to estimate for the completer sample the individual end of treatment means for each of the measures with a precision of ± 0.2 standard deviations, and the difference in change from baseline (pre to immediate post treatment) for the outcome domain measures with a precision of ± 0.3 standard deviation units.

Both the standard deviation and the distribution of costs are presently unknown for the type of patients who will be enrolled in Telepsychology. Thus, it is difficult to obtain a meaningful estimate of the power to detect a difference in CE from any arbitrary value. We propose to determine costs and apply to our economic model after the completion of the study, and then use the bootstrap technique to obtain a 90% Confidence Interval (CI) around the estimated costs. The bootstrap technique is appropriate because, as noted, the distribution of costs for these types of patients is presently unknown.

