#### Additional Analyses

In additional analyses, using the intent-to-treat sample and the baseline (week 0), mid- (week 4) and post- (week 8) active-treatment (randomized) phase values for continuous clinical variables (GDS, BAI, BDI, SF-36, patient ratings, functional status indicators), we will use random regression models (RRM) analyses (or equivalently, hierarchical linear model [HLM] or mixed effects models) to compare the Telepsychology and Same-Room conditions over the 8-week active phase time tracjectory. These analyses will use scores for each outcome as the dependent variable and delivery mode (treatment) and time (time by treatment) as the primary independent variables. The random regression approach estimates individual change in outcome for each subject in addition to estimating average change in outcome within each treatment population. Specifically, random regression models allow for measurement of subjects at different time points, missing data, and time varying or invariant covariates [68-74]. Further, longitudinal methods for binary outcomes [75-77] will be used to compare the Telepsychology and Same-Room conditions for the dichotomous outcome measure (MDD response status measured at weeks 4 and 8). Methods for categorical or ordinal outcomes [78-82] will also be applied where appropriate.

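### The primary GDS/BDI responder outcome is placed at both 12 months and 8 weeks, and the sample size covers only GDS response at post-treatment

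*Protocol article*

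**What the plan says.** Clinical Outcome Measures states: "The primary clinical outcome measure is the proportion (%) of patients who respond to treatment". It then gives the GDS/BDI classification two dates:

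- "treatment responders will be those that demonstrate, at 12-month follow-up, improvement of at least 50% on the total score"
- "defining treatment response as at least a 50% improvement from baseline to post-treatment level"

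Methods lists the assessments after mid-treatment as "post-treatment (8-weeks), 3-months, and 12-months", so post-treatment means 8 weeks and is not another name for the 12-month visit. Study Instruments and Data Collection Schedule uses the same labels.

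Sample Size Determination and Power Analysis uses one measure and one visit: "Treatment response is defined as at least a 50% improvement from baseline to post-treatment level on the GDS". Data Analysis, Primary Clinical Outcome, sets the margin and the one-sided 90% limit but names no visit.

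For the SCID, response means that MDD is no longer diagnosed. If the three measures disagree, the overall conclusion follows the two that agree. The SCID interviews "will be administered at baseline and 12-months by raters blind to subject condition", and Table 1 shows the same schedule.

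**The concern.** A non-inferiority claim should rest on one comparison fixed in advance. Here two careful readers could follow the text and test different things: response at 8 weeks, or response at 12 months. The two delivery modes could look alike at the end of treatment and differ a year later, or the reverse. Either result could be presented as the primary answer by citing this protocol.

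The stated 85% power also attaches to only one of the possible primaries. If the primary is at 12 months, the powered endpoint is at the wrong visit. If it is at post-treatment, the powered endpoint is GDS alone, while the outcome section relies on GDS, BDI and SCID with a concurrence rule.

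**Working it through.** **1. The stated sample size reproduces.** Inputs from Sample Size Determination and Power Analysis: P = 0.70 in both arms, Δ = 0.15, one-sided α = 0.10, power 0.85.

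n per arm = (z₀.₉₀ + z₀.₈₅)² × 2P(1−P)/Δ² = (1.2816 + 1.0364)² × 0.42/0.0225 = 100.3.

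The protocol states about 100. Power at n = 100 is Φ(0.15/√(0.42/100) − 1.2816) = 0.849. Inflation for 10% without post-baseline data is 100/0.90 = 111.1, so 112. The arithmetic is right for post-treatment GDS response with P = 0.70.

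**2. Which measures exist at which visit (Table 1).**

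| | 8 weeks | 12 months |
|---|---|---|
| GDS | yes | yes |
| BDI | yes | yes |
| SCID | no | yes |
| Two measures can agree | yes (GDS, BDI) | yes |
| A third measure can settle a GDS/BDI split | no | yes |

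**3. Power if the primary is at 12 months.** The protocol gives no 12-month response rate, so the rates are assumptions. Equal true rates, Δ = 0.15 and one-sided α = 0.10 are kept. Power = Φ(0.15/√(2P(1−P)/n) − 1.2816).

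| Assumed rate | Power, 100/arm | Power, 80/arm | n/arm for 85% |
|---|---|---|---|
| 0.70 | 0.85 | 0.78 | 101 |
| 0.65 | 0.83 | 0.76 | 109 |
| 0.60 | 0.81 | 0.74 | 115 |
| 0.55 | 0.80 | 0.73 | 119 |
| 0.50 | 0.80 | 0.73 | 120 |

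The 80 per arm is the protocol's completer sample after 20% dropout. If instead those 20% are counted as non-responders, 0.70 × 0.80 = 0.56, and power with 100 per arm is 0.80. At an assumed rate of 0.75, power with 100 per arm is 0.88.

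**4. False non-inferiority rate if the visit stays open.** Simulation with true response 0.70 (Same-Room) and 0.55 (Telepsychology) on every endpoint, 100 per arm. A test passes when the one-sided 90% upper limit for the difference is at most 0.15. A single test passes in about 10% of trials. The latent correlation between endpoints is an assumption.

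| What may support the claim | ρ = 0.5 | ρ = 0.7 | ρ = 0.9 |
|---|---|---|---|
| GDS response at either visit | 18% | 18% | 16% |
| Concurrence kept, free choice of visit (GDS and BDI at 8 weeks, or two of three at 12 months) | 7% | 9% | 10% |

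Repeat runs put the first row at 16–19% and the second at 7–10%. For two independent tests the first row would be 1 − 0.90² = 19%.

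**The case against.** The strongest defence is that the concurrence rule already limits selective claiming. This stands in part. With agreement of two measures required, a free choice of visit leaves the error at about 7–10%, no higher than nominal. GDS and BDI agreement can also be assessed at 8 weeks; only the third measure that would settle a split is missing. The defence does not say which visit is primary, and the sample size paragraph uses GDS alone without that rule.

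Four stronger readings are tempting, but the protocol does not support them:

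- **Any one of five results could be claimed** (GDS and BDI at 8 weeks; GDS, BDI and SCID at 12 months), with a false-claim rate of about 31–35% at correlation 0.7–0.5. The protocol has no such rule; it requires two measures to agree.
- **A third, continuous primary outcome.** The sample size section does attach the primary label to a quantity "which measures the difference in change from baseline (pre to immediate post treatment) for the continuous outcome domain measures". That is a label slip in a statement about precision, with no margin or test. The outcome, sample size and primary analysis sections all name the proportion of responders, and Secondary Analyses lists the continuous changes.
- **Response status at weeks 4 and 8 contradicts the SCID schedule.** Additional Analyses never says that this status comes from the SCID, and GDS and BDI are available at both visits.
- **The trial is underpowered.** The calculation reproduces. Any loss of power at 12 months depends on rates that the protocol does not give.

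The conflict is also not something left to an analysis plan. Two statements in one section disagree, and the primary analysis section does not choose between them.

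**Conclusion.** The concern holds as a conflict of definition. The primary GDS/BDI responder classification has two visits, the sample size uses GDS at one of them, and the three-measure rule works fully only at the other. On either reading the powered endpoint is not the defined primary: it differs in time point if 12 months is meant, and in measure if post-treatment is meant.

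The size depends on what is allowed to carry the claim: about 16–19% false non-inferiority at the margin if GDS response at either visit suffices, and about 7–10% if two-measure concurrence is kept. These figures rest on assumed correlations of 0.5–0.9 and a true 15-point deficit on every endpoint. The wording must be settled because the primary question currently has two legitimate answers.

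**What to change.** Name one primary visit and one decision rule, and use them in Clinical Outcome Measures, in the sample size section and in Primary Clinical Outcome. Two repairs are coherent:

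- **(a) 12 months.** GDS, BDI and SCID are all available and the two-of-three rule applies in full. Make 8-week response secondary. Restate P and power for 12 months: about 80–85% with 100 per arm for rates of 0.50–0.70, and about 73–78% with 80 per arm. Intervention and Control Groups says that data on patients given further treatment during follow-up will be analysed separately; reconcile that with the intention-to-treat analysis.
- **(b) 8-week GDS response.** This keeps 100 evaluable and 112 randomized per arm, with 85% power. Rewrite Clinical Outcome Measures so that 12-month response and the SCID-based rule are secondary.

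Under either option, relabel the continuous change score in the sample size section as secondary, in line with Secondary Analyses.

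The cost is wording. Option (a) also brings a somewhat less favourable power figure if the assumed 12-month rate is below 0.70; keeping 85% at rates of 0.65–0.50 would need 109–120 evaluable per arm. Neither option adds visits or measurements.

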### Data Analysis

#### Primary Clinical Outcome

Testing the non-inferiority of the Telepsychology mode of delivery to the standard Same-Room mode in terms of % responders can be carried out through either a confidence interval approach or through a modified hypothesis testing procedure [55-62]. For both approaches, a conclusion that the two modes of delivery are similar in clinical efficacy (non-inferior) requires that the response proportion (% responders) for the standard delivery (Same-Room) cannot exceed by more than Δ the response proportion for the novel delivery (Telepsychology). We assume Δ = 0.15 between the novel delivery and the standard delivery (one-sided non-inferiority). With the confidence interval approach, the upper limit of the one-sided 90% confidence limit for the difference in % responders for the novel delivery (Telepsychology) and the standard delivery (Same-Room) must be 0.15 (Δ) or less to accept the hypothesis of a non-inferior novel treatment. Statistically, this translates into testing a non-zero difference between the treatments, where noninferiority is established by demonstrating that the difference between treatments is less than the maximum clinically unimportant difference in response proportions, Δ[55-57,59,61,62]. The hypothesis testing approach to evaluating equivalency in % responders, with an appropriately adjusted test statistic as described by Dunnett and Gent [56] and Farrington and Manning [57] will also be used.

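### The rule that two of three depression measures decide the trial does not match the GDS-only sample size, and its error is not guaranteed at the stated 10%

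*Protocol article*

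**What the plan says.** Under Clinical Outcome Measures, the primary clinical outcome is the proportion of responders, and "Treatment Responder status will be determined using each of the dependent measures of depression": the GDS, the BDI and the SCID. GDS and BDI response is a 50% improvement in score; SCID response is no longer having the MDD diagnosis. Each measure is analysed and reported separately. Where the analyses disagree, "overall conclusions regarding treatment response will be based on the two measures that concur". This is stated as an a priori position.

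Sample Size Determination and Power Analysis uses one measure only: "Treatment response is defined as at least a 50% improvement from baseline to post-treatment level on the GDS". It sizes the trial "assuming Δ = 0.15, one-sided α = 0.10, P = 0.70, and power = 0.85", which gives about 100 analysed and 112 randomized per arm.

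Data Analysis, Primary Clinical Outcome, applies the one-sided 90% limit to the responder proportion without naming a deciding measure; the limit "must be 0.15 (Δ) or less to accept the hypothesis of a non-inferior novel treatment". The article nowhere gives GDS precedence over the other two measures or states an error rate for the concurrence rule. The Bonferroni correction under Additional Analyses belongs to a different, later set of analyses.

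**The concern.** Three pass/fail results always contain two that agree, so the concurrence sentence is an equal-weight majority vote. The stated alpha and power belong to a single test on GDS and do not carry over to a vote.

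Two things follow. First, if two measures are truly inferior by the margin and the third is not, the third will usually pass, and a chance pass on either of the other two then produces an overall non-inferiority conclusion. Second, GDS, for which the planning assumptions were made, can fail and be overruled by BDI and SCID. The trial's headline clinical claim depends on this rule.

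**Working it through.** **Inputs from the sample size section.** Same-Room response P = 0.70, margin 0.15, one-sided alpha 0.10, power 0.85, 100 analysed per arm, 10% loss.

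**Assumptions, since the article gives no figures.** P = 0.70 and margin 0.15 also for BDI and SCID; latent correlation between measures within a patient 0.2 to 0.8.

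**Step 1. Reproduce the stated sample size (GDS alone).**

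n = 2P(1−P)(z0.90 + z0.85)² / Δ² = 0.42 × (1.2816 + 1.0364)² / 0.0225 = 100.3 per arm, agreeing with the stated 100.

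Power at 100 per arm: standard error √(0.42/100) = 0.0648; Φ(0.15/0.0648 − 1.2816) = 0.849. Randomized: 100/0.90 = 111.1, rounded up to 112. The stated figures are right for one GDS test.

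**Step 2. The vote by hand, with independent measures.** A measure at the margin passes with probability 0.10; a truly equal one with probability 0.849.

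- All three at the margin: 3 × 0.1² × 0.9 + 0.1³ = 0.028.
- Two at the margin, third equal: 0.849 × (1 − 0.9²) + 0.151 × 0.1² = 0.161 + 0.002 = 0.163.
- Two at the margin, third certain to pass: 1 − 0.9² = 0.19, the worst case.
- GDS at the margin, other two equal: 0.1 × (1 − 0.151²) + 0.9 × 0.849² = 0.098 + 0.649 = 0.747.

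**Step 3. The vote with correlated measures.** Patient-level simulation: correlated binary outcomes, 100 per arm, Same-Room minus Telepsychology, Wald one-sided 90% upper limit at or below 0.15, latent correlation 0.2 to 0.8.

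| True state (Telepsychology minus Same-Room) | Vote declares non-inferiority |
|---|---|
| Two measures −0.15, third 0 | 17–18% |
| Two measures −0.15, third −0.05 | 13–15% |
| Two measures −0.15, third −0.10 | 8–13% |
| All three −0.15 | 4–8% |
| GDS −0.15, other two 0 | 74–77% |
| GDS −0.15, other two −0.05 | 41–46% |
| GDS −0.15, other two −0.10 | 15–20% |
| All three 0 (power) | 88–92% |

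In the fifth row, GDS fails and is outvoted in about 65% of trials. If the test statistics themselves are correlated 0.99, the two-at-the-margin case falls to 0.11, still above 0.10.

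**Step 4. The alternatives, same simulation.** GDS alone: error about 0.10, power 0.85. GDS plus at least one other: passing requires GDS to pass, so error at the GDS margin is at most about 0.10; power is about 0.82.

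**The case against.** The strongest reply is that the rule is pre-specified and transparent. Every measure is reported, so a failed GDS result would be visible, and when all measures are equal the vote raises power. It is also conservative when all three measures sit at the margin together. All of that stands.

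A reader might infer from the 74–77% figure that the rule has a false-positive rate near 75%. The article does not support that. It gives the three measures equal standing in the outcome section and ties GDS specifically to the sample size calculation. If BDI and SCID are truly equal between arms, a non-inferiority conclusion is the right answer to the question the vote asks. The figure shows a mismatch between the sized endpoint and the deciding rule; it would be a Type I error only if GDS were the sole primary endpoint.

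A reader might also take 17–18% as the rule's usual error. That figure needs two depression measures inferior by the full margin and a third with no difference, in the same patients. Smaller disagreement gives a smaller excess or none.

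Two further replies carry less weight. The sample size section remarks that alpha may be set at 0.1–0.2 in such trials, but the level it chose is 0.10. And the sentence following the rule, about converging data from at least two measures, could mean a composite responder defined per patient, which would be one test at 10%. But the rule itself speaks of the results of separate analyses, and a composite would still not be the GDS endpoint that was sized.

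**Conclusion.** The point holds as a mismatch between the decision rule and the sized endpoint, together with an error rate that is not guaranteed at 10%. Under the stated assumptions the vote's error runs from 4–8% with all three measures at the margin to 17–18% with two at the margin and the third equal; 19% is the bound when the third is certain to pass. Separately, GDS can be inferior by the full margin and be outvoted, with a frequency that depends strongly on how far the other measures diverge from it.

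The sizes rest on assumed response rates and margins for BDI and SCID and on assumed correlations. The lack of a guarantee does not depend on the particular values chosen. A reader might also infer that the sample size is wrong; it is not, since it reproduces for GDS alone. This should be fixed, but because the excess depends on discordant measures and the remedy is a change of wording, it does not rank as a must-fix.

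**What to change.** In Clinical Outcome Measures, make the GDS responder proportion the single deciding test at one-sided 10%, and report BDI and SCID response as supportive. The stated 100 analysed and 112 randomized per arm and the 85% power then stand unchanged.

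Alternatively, keep the concurrence rule but require GDS to be one of the two concurring measures, and restate power as about 82%. This holds the error at about 10% or less when GDS is at the margin. It does not do so for a null in which BDI and SCID are at the margin and GDS is equal, where about 16% would still pass with independent measures, so the text should say that the claim concerns GDS.

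Either way the cost is wording, with no extra patients or data. What is given up is the vote's power when all measures are equal: 0.88–0.92, against 0.85 for GDS alone or 0.82 for GDS plus one other.
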